## Abstract

Physical literacy is crucial for children’s appropriate development and physical, social and mental health. In a school setting, class-based physical activity (PA) interventions are considered to be appropriate programs to foster PA participation and cognitive development. The purpose of this project, named the Active Learning in PHYsical Literacy (ALPHYL) study, was to describe a multicomponent classroom-based physically-active learning randomised control trial (RCT) in primary school children. The main purpose was to promote children’s physical literacy, academic achievement and cognitive function. The ALPHYL study is mainly based on physical literacy, active school models and the Supportive, Active, Autonomous, Fair and Enjoyable principles. The ALPHYL is an 8–10-week RCT to be conducted in six primary schools (12 classes) in Valencia (Spain) and its metropolitan area. Schools will be randomly assigned to the intervention or waiting-list control group. After a 30 h in-person training course for teachers and weekly meetings in the three months of resource preparation, the ALPHYL intervention will be conducted in physical education (PE) and non-PE lessons by teachers. The intervention consists of at least three daily sessions of physically active learning in addition to model-based PE teaching. Its feasibility will be evaluated weekly according to the Reach, Effectiveness, Adoption, Implementation and Maintenance framework. To assess its effectiveness, a pre-test, post-test and retention (8–10 weeks post-intervention) with primary outcomes (i.e., PA level, motor competence, perceived motor competence and PL, motivation, perceived social support, academic achievement and cognitive function), secondary outcomes and covariates will be collected.

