## 2. Materials and Methods

### 2.1. Study Design and Participants

The Active Learning in PHYsical Literacy (ALPHYL) study is a RCT in primary schools in Valencia (Spain) and its metropolitan area, with the schools as the units of randomisation and the students as the units of analysis. The design, implementation and reporting of ALPHYL will be carried out according to the CONSORT statement [25] and considering the SPIRIT recommendations. The sample will consist of at least 264 primary school Grade 5 pupils (i.e., 10–11 years old).

The sample size was calculated from previous studies that focused on the effects of interventions on PA and motor competence [11,22], using G*Power 3.1 software (University of Düsseldorf, Düsseldorf, Germany). From these studies, for an effect size between 0.30 and 0.32 with an alpha level of 0.05 and statistical power of 90%, the sample size had to be between 105 and 220 participants. To avoid reducing statistical power due to experimental mortality, the sample was increased by 20%, with the participation of 264 children. To recruit the participants, children from six schools (three intervention and three control schools; four public and two private) in Valencia and its metropolitan area will take part, consisting of pupils willing to participate and whose families provide signed informed consent (inclusion criterion). Pupils who present evident physical and mental difficulties that prevent them from satisfactorily completing all the measurements proposed in the study will not be included in the analyses (exclusion criteria). Only typically developing children will be included in the analysis.

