### 2.3. Procedure

The CONSORT study flow diagram is shown in Figure 1. A list of primary schools in Valencia and its metropolitan area will be obtained from the government educational institutions. The schools will be randomly selected and ordered in a list using computer-generated random numbers by a researcher from the study team. The inclusion criteria for the schools’ participations will be: (a) must have at least two groups of primary school Grade 5 pupils, and the teachers involved in both must agree to participate; (b) each class group includes at least 75% of the participants; and (c) children must not have taken part in other PA promotion interventions during the intervention period in the previous two years. If a school decides not to participate, the same procedure will be performed with the next school selected from the list. The six selected schools will also be randomly allocated to the intervention (*n* = 3) or control groups (*n* = 3). Students will be unaware of whether they have been allocated to the intervention or control group.

In order to detect barriers to and facilitators of the intervention’s adoption, implementation and sustainability, an instrument based on the reach, effectiveness, adoption, implementation and maintenance (RE-AIM) tool will be used to analyse its reach, effectiveness, adoption, implementation and maintenance [26], as well as its impact [8,26]. This instrument will be implemented with the teachers involved in the intervention, who will provide information on their teaching methods and the pupils’ participation by completing a personal teaching diary [13,27].

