### 2.4. Intervention

The intervention will last for approximately 8–10 weeks. Systematic review evidence by Norris et al. [11] indicated that if the duration lasts longer than 8 weeks and the total volume in minutes is less than those proposed in the current study, the acute effects on some of the main variables (e.g., PA or academic achievement) could be reduced. Another recent school-based intervention [28] conducted over 8 weeks found positive effects on motor competence. To ensure that all the groups receive a similar amount of physically active learning, three research assistants with expertise in PE and classroom-based physically active learning will accompany the teaching team during the entire intervention. Their role will be to support, assist and collaborate in the development of resources, monitor their implementation, and ensure that the lessons are delivered according to the study’s guidelines.

In addition to the PE lessons, at least three physically active activities in subjects other than PE will be conducted every day (5 days per week), with a total duration of approximately 30 min of light and MVPA per day. The weekly dose of physically active learning will thus be 100–150 min, so that a volume of 800–1200 min is foreseen during the 8–10 weeks. All three of the physically active lessons per day consisted of transforming and delivering traditional teaching in maths, science, social science, language, etc., by including a movement-based activity in the work program. No instant restriction will be used for physically active learning. For instance, during a typical lesson of science wherein pupils are sitting in their chairs, the classroom teacher and the research assistant will propose them to move to the corridor, hall or any available open space to conduct the physically active activity. Conversely, in the control schools, the whole teaching process will be conducted in a regular manner following the formal curricula, which traditionally involves having the pupils sit for the whole lesson.

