The PE classes at both the intervention and control schools will also be conducted following the formal curricula. On the one hand, at intervention schools, PE will be based on a hybridisation of cooperative learning, non-linear pedagogy and health-based PE [29,30,31,32], which are in accordance with the current law of education. On the other hand, at control schools, PE teachers will deliver their own traditional program that is also based on the law of education (i.e., personal knowledge and autonomy, fundamental movement skills, corporal expression, physical activity and health, and sport and games).

The promotion of physical literacy will be based on increasing motor competence, as well as self-perception and motivation for PA, positive affective within the group (e.g., enjoyment and fun), interdisciplinary knowledge (i.e., specific content of physically active lessons and PE) and a sense of personal and social responsibility. To foster healthy interpersonal skills, teaching quality will be enhanced by a coherent sense of identity, the ability to act as a responsible, moral and social member of the group [33], and the learners’ holistic development. Supportive, Active, Autonomous, Fair and Enjoyable (SAAFE) principles [34] will be the basis of the intervention.

To encourage family support for PA practice and a healthy lifestyle, three reports will be sent to the families during the intervention to share behavioural change recommendations for the following: first, playing with the children using novel easy-to-construct materials; second, assessing psychosocial support for the children; and third, actively travelling to the school. From the third week of intervention, teachers will share each report with the families by using the social media (i.e., Telegram) they commonly use to communicate with them 15 days apart. The reports will be available on the ALPHYL webpage.

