### 2.6. Data Management and Statistical Methods

To avoid possible bias in the data analysis, an independent blinded researcher will carry out a pseudonymisation process to guarantee the anonymity of the data. Missing data will be imputed using multiple imputation. According to our Institutional Review Board (IRB), a data monitoring committee will not be necessary since this is a low-risk study. Adverse events and protocol deviation will be documented by teachers using their personal teaching diary. Moreover, the research team will perform weekly audits to ensure data quality and the correct development of the protocol.

Independent researchers will also code actual motor competence videotapes so that they are stratified and counterbalanced. The video coded data, information from the individual questionnaires, accelerometer data and a family proxy-report of the participants’ residential neighbourhood will be hosted on an open access digital platform (zenodo.org) to be available to the scientific community.

The teachers’ data obtained in the semi-structured interviews will be categorised and thematically analysed by the NVivo^®^ qualitative analysis program (QSR International: Technology & Software Solutions, Burlington, MA, USA).

Structural equation modelling will be conducted to analyse the association and mediating role of some of the measured variables according to the conceptual models of children’s motor development and physical literacy [21,66]. To study the effect of the intervention on primary and secondary variables, linear mixed models will be built with the time, condition and interaction of time and condition as fixed effects, adjusting for baseline values. When a significant interaction effect is found, post-hoc tests will be applied by the least significant difference method. The data will be analysed on different statistical software, mainly SPSS (SPSS Inc., Chicago, IL, USA) and Mplus [67].

An analysis of the intervention effects in a person-centred approach will allow us to determine the children’s profiles according to their primary physical literacy outcomes (i.e., actual and perceived motor competence, motivation, perceived social support and cognitive function), while the trends and association will be analysed with the remaining physical literacy primary and secondary outcomes, for which self-organised maps will be created on MATLAB (MathWorks Inc., Natick, MA, USA).

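### The plan says pupils will be unaware of their allocation, but its open intervention rules this out for intervention pupils, and three of seven primary outcome rows are pupil self-report

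*Protocol article*

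**What the plan says.** The blinding statement stands in Section 2.3, directly after the allocation of the six schools: "Students will be unaware of whether they have been allocated to the intervention or control group". It carries no qualifier, such as a restriction to the hypotheses or to the existence of another arm.

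Allocation is by school, "with the schools as the units of randomisation and the students as the units of analysis" (Section 2.1), and the Abstract names the comparator: "Schools will be randomly assigned to the intervention or waiting-list control group".

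Section 2.4 describes what intervention pupils receive. In an ordinary lesson the teacher and a research assistant "will propose them to move to the corridor, hall or any available open space". PE in these schools follows a hybrid of several pedagogical models, while control PE teachers keep their own programme. In addition, "three reports will be sent to the families during the intervention". Control schools otherwise teach in the regular way.

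Table 2 lists the primary outcomes. Section 2.5 says that perceived motor competence, physical literacy, motivation and perceived social support are collected by a questionnaire that pupils complete in the classroom. Section 3 names one main limitation, the lack of maturity assessment, and does not mention blinding.

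**The concern.** The procedures in Section 2.4 contradict the sentence in Section 2.3. Pupils taken out of their seats several times a day for two months, with an additional adult present, know which condition they are in, whether or not anyone gives them its label.

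What is at stake is how the self-reported primary outcomes are read. Section 2.4 says that the intervention aims to raise self-perception and motivation for physical activity, and one of the family reports concerns psychosocial support for the child. The questionnaires ask pupils about closely related things. A pupil who knows that the school has put effort into this may answer more favourably for that reason alone, and control pupils have no matching prompt. Such an effect can differ by arm and would be added to any true effect. A reader who takes Section 2.3 at face value, and finds nothing on the subject in Section 3, could conclude that participant blinding guards against this.

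**Working it through.** The plan gives no figure to reproduce. The check sets the blinding statement against the procedures and makes two counts.

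**1. Statement against procedures**

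| Feature | Intervention schools | Control schools | Where |
|---|---|---|---|
| Active learning outside PE | At least 3 activities a day, 5 days a week, 8–10 weeks | None; regular teaching | 2.4 |
| Research assistant in lessons | Yes | Not described | 2.4 |
| PE | Hybrid of several models | Teachers' own traditional programme | 2.4 |
| Reports to families | Three | Not described | 2.4 |
| Sham or attention control | Not applicable | Not described | 2.4 |

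Each of these differences can be seen by a pupil or the family, and nothing in the control arm imitates them.

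**2. Visible exposure before the post-test**

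Sessions per intervention pupil = activities per day × days per week × weeks.

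- 8 weeks: 3 × 5 × 8 = 120
- 10 weeks: 3 × 5 × 10 = 150

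Three a day is the plan's stated minimum, so these are minimum counts for each duration. Control pupils are scheduled for none.

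**3. Primary outcome rows in Table 2, by source of measurement**

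- Pupil self-report: perceived motor competence and physical literacy; motivation; perceived social support. That is 3 rows.
- Device or test: physical activity level (accelerometer); actual motor competence (CAMSA); cognitive function (Stroop and Digit Span). That is 3 rows.
- School grades: academic achievement. That is 1 row.

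3 + 3 + 1 = 7 rows, of which 3/7 (43%) are pupil self-report.

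**4. Whether other masking fills the gap**

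Section 2.6 has a blinded researcher pseudonymise the data. That protects data handling. It cannot protect a questionnaire answer, because the pupil is the assessor of that outcome.

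**5. Result**

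For intervention pupils, the statement in 2.3 and the procedures in 2.4 cannot both hold. If one arm knows what it is receiving, the comparison of self-reports is not blinded, whatever the other arm knows.

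**The case against.** The best defence is that the sentence concerns awareness of allocation, not of activities. Whole schools are randomised, so all study pupils in a school share one condition. Ten- and eleven-year-olds may experience new lessons without hearing of a comparison, an arm label or a hypothesis. Control pupils have ordinary lessons and might never learn that another arm exists. This stands in part: the contradiction is firm for intervention pupils and no more than likely for control pupils. It does not rescue the sentence, because the text does not give the narrower meaning and the expectation problem needs only one aware arm.

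A second defence is that the plan nowhere says the self-reported outcomes are protected from bias, does not list blinding among its strengths, and commits to CONSORT reporting. That is correct. The misleading impression arises from an unqualified sentence combined with silence in Section 3, not from an explicit claim.

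Three stronger readings are tempting, and the documents do not support them.

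- A reader might infer that consent itself unmasks the arms. Section 2.1 says only that participants are "pupils willing to participate and whose families provide signed informed consent". What the consent form discloses about a waiting list is not shown.
- A reader might infer that the motor competence coders are unmasked, because they are called independent and not blinded. Section 2.6 says: "Independent researchers will also code actual motor competence videotapes so that they are stratified and counterbalanced". A condensed article may leave coder masking to the full protocol, so silence here shows nothing.
- A reader might infer that the self-reports should become merely supportive. Physical literacy is a main purpose of the trial, and Section 1 defines it partly through motivation and confidence. Re-ranking the outcomes is a trade-off for the investigators and does not follow from the blinding error. An open trial can keep self-reported primary outcomes if it says plainly what they are.

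**Conclusion.** The point holds. Section 2.3 states a masking property that the design in Section 2.4 does not have, at least for the three intervention schools. It bears on three of the seven primary outcome rows. The device- and test-based rows are less exposed.

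The size of any resulting bias cannot be derived from the documents, and none is claimed. The expectation effects are best described as possibly differing by arm. It would go too far to say that they act in one arm only, since control pupils who knew they were waiting might also answer differently.

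The conclusion rests on two assumptions: that the intervention is delivered roughly as scheduled, and that pupils notice it. It does not depend on what families were told at consent, on what control pupils know, or on how the videos are coded. Randomisation, measurement and the analysis model are unaffected. What is wrong is the stated blinding status and the missing limitation.

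**What to change.** - **Section 2.3.** Replace the sentence with one saying that pupils are not blinded to the condition they receive. If it is true, add that pupils are not told the study hypotheses or about the other condition.
- **Section 3.** Add unblinded pupil self-report as a limitation, naming perceived motor competence and physical literacy, motivation and perceived social support.
- **Interpretation.** State that effects on these three rows will be read with that caution and alongside the device- and test-based outcomes. Keep the primary outcome set unchanged.

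The cost is a few sentences. Sample, schedule, intervention and analysis model stay as they are. The downside is that the report can claim less from the self-reported outcomes, which the open design already implies.

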### 2.4. Intervention

The intervention will last for approximately 8–10 weeks. Systematic review evidence by Norris et al. [11] indicated that if the duration lasts longer than 8 weeks and the total volume in minutes is less than those proposed in the current study, the acute effects on some of the main variables (e.g., PA or academic achievement) could be reduced. Another recent school-based intervention [28] conducted over 8 weeks found positive effects on motor competence. To ensure that all the groups receive a similar amount of physically active learning, three research assistants with expertise in PE and classroom-based physically active learning will accompany the teaching team during the entire intervention. Their role will be to support, assist and collaborate in the development of resources, monitor their implementation, and ensure that the lessons are delivered according to the study’s guidelines.

In addition to the PE lessons, at least three physically active activities in subjects other than PE will be conducted every day (5 days per week), with a total duration of approximately 30 min of light and MVPA per day. The weekly dose of physically active learning will thus be 100–150 min, so that a volume of 800–1200 min is foreseen during the 8–10 weeks. All three of the physically active lessons per day consisted of transforming and delivering traditional teaching in maths, science, social science, language, etc., by including a movement-based activity in the work program. No instant restriction will be used for physically active learning. For instance, during a typical lesson of science wherein pupils are sitting in their chairs, the classroom teacher and the research assistant will propose them to move to the corridor, hall or any available open space to conduct the physically active activity. Conversely, in the control schools, the whole teaching process will be conducted in a regular manner following the formal curricula, which traditionally involves having the pupils sit for the whole lesson.

The PE classes at both the intervention and control schools will also be conducted following the formal curricula. On the one hand, at intervention schools, PE will be based on a hybridisation of cooperative learning, non-linear pedagogy and health-based PE [29,30,31,32], which are in accordance with the current law of education. On the other hand, at control schools, PE teachers will deliver their own traditional program that is also based on the law of education (i.e., personal knowledge and autonomy, fundamental movement skills, corporal expression, physical activity and health, and sport and games).

The promotion of physical literacy will be based on increasing motor competence, as well as self-perception and motivation for PA, positive affective within the group (e.g., enjoyment and fun), interdisciplinary knowledge (i.e., specific content of physically active lessons and PE) and a sense of personal and social responsibility. To foster healthy interpersonal skills, teaching quality will be enhanced by a coherent sense of identity, the ability to act as a responsible, moral and social member of the group [33], and the learners’ holistic development. Supportive, Active, Autonomous, Fair and Enjoyable (SAAFE) principles [34] will be the basis of the intervention.

To encourage family support for PA practice and a healthy lifestyle, three reports will be sent to the families during the intervention to share behavioural change recommendations for the following: first, playing with the children using novel easy-to-construct materials; second, assessing psychosocial support for the children; and third, actively travelling to the school. From the third week of intervention, teachers will share each report with the families by using the social media (i.e., Telegram) they commonly use to communicate with them 15 days apart. The reports will be available on the ALPHYL webpage.

Table 1 shows the intervention program. The classroom teachers involved will be accompanied on two fronts: by the school’s PE teachers and a research assistant who will act as a guide and/or reference to organise physically active learning. On the other hand, the co-created resources (i.e., cards, sheets or any required resource in the physically active learning activities) will be made available to them. PE and other teachers will receive training and support for the implementation of the trial. They will be provided with the proposals that will be explained, put into practice and evaluated during the training course. Before and after the trial, two semi-structured focus-group meetings will be conducted with the teachers involved.

